### Intervention

**Ketamine** will be supplied in 2 ml glass ampoules containing 15 mg in 1 ml and supplied in numbered treatment packs containing 3 ampoules (up to 2 for administration and 1 in case of breakage).

**Morphine** will be supplied in 2 ml glass ampoules containing 10 mg in 1 ml and supplied in numbered treatment packs containing 3 ampoules (up to 2 for administration and 1 in case of breakage).

Trial IMP was manufactured and supplied by ModePharma Ltd, an MHRA licenced company who specialise in producing medications for clinical trials. The IMP is supplied in a standard white cardboard ampoule box.

### Dosing regime

The trial drug is prepared by diluting one ampoule of trial drug (either ketamine or morphine) with 9 ml of 0.9% sodium chloride in a 10 ml syringe. The trial drug is then administered by slow IV or IO injection, titrated to effect over five minutes (i.e. approximately 2 ml aliquots per minute), aiming to give the minimal effective dose.

If the patient still reports pain 5 min after receiving the first full syringe, the paramedic will prepare a second syringe of trial drug in the same manner. Further trial analgesia will be administered in 2 ml aliquots every 5 min until adequate pain relief is achieved, or all 10 ml of the second syringe has been administered.

The maximum volume of trial drug that can be administered is 20 ml (2 syringes), while the maximum dose that can be administered is 30 mg (two ampoules) of ketamine or 20 mg (two ampoules) of morphine. In standard practice, paramedics carry 2 × 10 mg in 1 ml ampoules of morphine. The maximum dose of morphine that a paramedic can administer is 20 mg (or two syringes). The rate of administration in the trial mirrors standard practice. Consequently, if a trial paramedic happened to open a drug pack containing morphine, then the patient would receive morphine in the exact same manner as standard practice.

The study is intended to compare morphine and sub-dissociative ketamine. Unfortunately, no morphine equivalent dose for ketamine has been published. Bredmose et al. [22] published a paper in a UK trauma population reporting a ketamine analgesic dose of 0.1 mg/kg. Currently, only specialist prehospital teams are able to administer ketamine for analgesia in the UK. The locally recommended dose is 0.2 mg/kg, which can be repeated up to a maximum of 0.5 mg/kg. Two studies by Motov [35, 36] used a dose of 0.3 mg/kg, but reported dissociative effects in some patients.

We wanted to minimise the likelihood of dissociative effects. Based upon mean UK adult weights (85.1 kg for males and 71.8 kg for females) we estimated that an average male would receive approximately 0.18 mg/kg from one syringe containing 15 mg ketamine, with the potential for further analgesia up to 0.36 mg/kg by administering the second syringe. Our approach of titration to effect (standard practice) should minimise the risk of larger dissociative doses being administered. More recent reviews by Riccardi et al. [37] and Sandberg et al. [38] have respectively recommended analgesic doses of 0.15–0.3 mg/kg and 0.1–0.2 mg/kg for ketamine. We therefore believe this dosing regime is consistent with the available evidence.

## Outcomes

Table 2 presents the timings of when study outcome measures will be collected. Table 3 details the definition and methods to calculate the study outcomes.

**Table 2 Tab2:** Schedule of delivery of intervention and data collection

Visit	1	2	3	4
Visit Window (No. Weeks ± No. Days)	Baseline/Pre hospital/Hospital arrival	After hospital arrival	3 m (± 2w)	6 m (± 1 m)
Trial Information	✓	✓		
Informed consent		✓		
Randomisation	✓			
Vital signs	✓			
Inclusion/exclusion criteria	✓			
Intervention	✓			
Rescue analgesia	✓			
Quality of Life—EQ-5D-5L			✓	✓
Side effects & Adverse events	✓	✓	✓	✓
Questionnaire—BPI-SF			✓	✓
Questionnaire—CSRI			✓	✓
SPID	✓			
TOTPAR	✓			
Time to perceptible analgesia	✓			
Time to meaningful analgesia	✓			
Time to peak analgesia	✓			
Duration of analgesia	✓			
Patient Global Impression of Change	✓			
Resource use	✓	✓	✓	✓

**Table 3 Tab3:** Outcome measure definitions

	Definition	Mitigations
*Primary outcome*		
Effectiveness of pain relief from randomisation to arrival at hospital as measured by Sum of Pain Intensity Difference (SPID) score (using a 0–10 numerical rating scale)	The SPID is measured using a weighted sum of the scores, as shown below: $$SPID_{n} = \mathop \sum \limits_{i - 1}^{n} \left( {T_{i} - T_{i - 1} } \right)*PID_{i}$$ *T*_*i*_ is the time in hours when observation *i* is taken *PID*_*i*_ is the difference in Pain Intensity (PI) scores from initial pain score to the pain score at time *T*_*i*_. The SPID looks to calculate the area under the curve of pain intensity different over time	
*Secondary outcomes*		
The Total Pain Relief (TOTPAR)	The TOTPAR is measured using a weighted sum of the scores, as shown below: $${TOTPAR}_{n}= \sum_{i-1}^{n}\left({T}_{i}-{T}_{i-1}\right)*{PAR}_{i}$$ *T*_*i*_ is the time in hours when observation *i* is taken *PAR*_*i*_ is the pain relief score measured as defined below on a scale of 1 to 3 We measure minimal pain relief as 1.8 (1.7–1.9) change in pain score, much pain relief as 4.0 (3.9–4.1) and very much pain relief as 5.2 (5–5.4) Percentage changes defined as 20.3 (19–21.6), 44.4 (43.2–45.6), 56.1 (53.9–58.4) respectively	
Time to Perceptible Analgesia	Perceptible pain relief is defined as a 20% change in NRS pain score from the initial pain score. The time will be taken as time of perceptible analgesia minus time of first administration	If 20% change not achieved, we will score this as perceptible analgesia not achieved
Time to Meaningful Analgesia	Defined as a 44% change in NRS pain score from initial pain score. The time will be taken as time of meaningful analgesia minus time of first administration	If 44% change not achieved, we will score this as meaningful analgesia not achieved
Time to Peak Analgesia	Measured as the time when lowest NRS pain score, relative to initial pain score, is achieved minus time of first administration	
Duration of Analgesia	Measured as the time period in which patient pain scores have consecutively decreased or remained stationary (There may be different instances of this per patient)	
Requirement for Rescue Analgesia	We will record whether a patient has needed rescue analgesia and which analgesia was administered, Entonox, paracetamol, ibuprofen, or other	
Proportion of patients with pain intensity score below 4/10 on NRS scale	At hospital arrival the research paramedic will record a NRS pain score. We will provide the proportion, as a percentage, of each patient that achieved a score < 4/10	If there is no hospital arrival score, we will use the scores recorded in the ambulance journey
Vital Signs	At each observation time, the respiratory rate (bpm), oxygen saturations (%), heart rate (bpm), blood pressure (mmHg) and their Glasgow Coma Scale (GCS)	
Glasgow Coma Scale	Three subscales measuring eyes, verbal, and motor response of each patient. The scales are as such: Eyes 1–4 Verbal 1–5 Motor 1–6	
Global Impression of Change	Using a 7-point Likert scale. The options offered ranging from ‘very much improved’ to ‘very much worse’	
Side effects and adverse events	Measured in the following categories, ‘Airway’, ‘Respiratory’, ‘Cardiovascular’, ‘Neurologic’, and ‘other’	
Ambulance job cycle time	Time taken from arrival on scene to hospital arrival	
Number of ambulance resources	Number of doctors, paramedics, doctors, and vehicles attending scene	
Cumulative IMP doses administered	Total dose of IMP administered	
CT scan use	If patient had a CT scan and how many	
Hospital or ICU admission	Yes; no option if patient is admitted to hospital or ICU	
Length of stay in ED, ICU, or hospital	Classed as date and time of admission to date and time of discharge	
BPI-SF at 3 and 6 Months		
9 part self-reported form which allows us to monitor the severity of the patient’s pain and its effect on their daily life. Split into two sections, pain intensity and pain inference	9 part self-reported form which allows us to monitor the severity of the patient’s pain and its effect on their daily life	
Pain Intensity	The pain severity part assesses the pain of the patient at its worst, least, average and now	We can then determine the average of the 4 categories to determine pain intensity, however it is recommended that we present all 4 of the options
Pain Interference	The interference section measures the effect of pain in 7 different tasks, walking, work, mood, enjoyment of life, relations with others, and sleep	Measure as a mean if at least 4 of the sections have been completed

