### Trial design and setting

This is a multi-centre, randomised controlled, double blinded trial comparing the clinical and cost-effectiveness of ketamine and morphine for severe pain following acute traumatic injury. It is a pragmatic, phase III trial working with two large NHS ambulance trusts with an internal pilot, aimed at mirroring existing practice of dealing with severe pain following acute traumatic injury. Participants will be followed up for 6 months. Adult patients (> = 16 years old) will be eligible for recruitment if they report severe pain following acute injury, in the pre-hospital environment and are determined by a paramedic to require parenteral morphine or equivalent.

The trial has been designed to determine if ketamine is superior to morphine as a prehospital analgesic. The prehospital phase ends once the patient arrives at hospital.

Randomisation will occur when the trial drug-pack is opened. The trial drug pack includes three ampoules of trial drug containing either ketamine of morphine. The ampoules of ketamine and morphine appear identical. The treating paramedic will not know which drug they are administering, hence the double blinding.

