### Primary outcome

Effectiveness of pain relief from randomisation to arrival at hospital as measured by Sum of Pain Intensity Difference (SPID) score (using a 0–10 numerical rating scale(NRS). As this is a pragmatic trial, no fixed time interval was specified to record pain scores, however we did request that pain scores were documented regularly from the point of initial IMP administration to arrival at the hospital.

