### Secondary outcomes

*Effectiveness of pain relief and overall patient experience from randomisation to arrival at hospital*
Total Pain Relief (TOTPAR) scoreTime to perceptible analgesiaTime to meaningful analgesiaTime to peak analgesiaDuration of analgesiaRequirement for rescue analgesiaProportion of patients with a pain intensity score below 4/10 (0–10 numerical rating scale (NRS)) on arrival at hospitalVital signs (oxygen saturation, blood pressure, heart rate, respiration rate, Glasgow Coma Scale)Patient Global Impression of Change on arrival at hospital

*Incidence of side effects and adverse events*
Airway: vomiting, aspiration, advanced airway managementRespiratory: desaturation, need for ventilatory supportCardiovascular: arrhythmia, hypotension and hypertensionNeurologic: sedation, excitatory movements, adverse behavioural reactionsOther: nausea, allergic reaction

*Resource use*
Ambulance job cycle time (scene arrival to arrival at hospital)Number of ambulance resources (technicians, paramedics, doctors and vehicles) in attendanceCumulative IMP doses administeredCT scan useHospital or ICU admissionLength of stay ED, ICU, Hospital

*Longer term outcomes*
Chronic pain using Brief pain inventory-short form (BPI-SF) at 3 & 6 months from randomisationHealth-related quality of life measured using the EQ-5D-5L at 3 and 6 months from randomisationCost-effectiveness expressed in terms of incremental cost per quality-adjusted life year (QALY) gained

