### Data analysis

The statistical analysis will follow the estimand framework [46]. Primary analysis will be by intention to treat. The primary outcome will be the SPID, a measure of the area under the curve of the pain score difference from baseline over time. The primary outcome will be analysed using a linear regression. Both unadjusted and adjusted (for important covariates) estimates and 95% confidence intervals for the treatment effect will be obtained. The adjusted estimates will form the basis for the primary analysis. Descriptive summaries of the outcomes will be presented as frequencies or means and medians. For the adjusted estimates, the covariates used will be age (< 60; ≥ 60 years), gender, weight and alternative parenteral IV paracetamol prior to randomisation (as a dichotomy split by yes or no). Age and gender have been chosen as covariates as these groups can experience pain differently, administration of IV paracetamol prior to randomisation is included as a covariate as it is an adjunctive treatment that may impact pain response. Weight is included as a covariate since different weight groups have different requirement for an adequate dose of IMP. For continuous secondary outcomes, analysis will be carried out in a similar way to the primary outcome. For categorical outcomes, logistic regression models will be used. Participant vital signs are recorded in a longitudinal format, for these outcomes we will use a mixed effect model.

Various intercurrent events have been identified for this trial, in line with the estimand framework [46], and approaches to dealing with these have been considered. For discontinuation of the allocated treatment and use of rescue analgesia, we will follow the treatment policy, where the data is analysed as observed. Compliance with administration of the trial drug as per the trial protocol will be monitored. If there is a noticeable degree of non-compliance, we will carry out a complier average casual effects (CACE) analysis [47, 48]. If sufficient data permits, sensitivity analysis will be conducted on a modified intention to treat population, excluding participants that were randomised but the drug was not given. Again, if sufficient data permits, participant deaths will be analysed using Pocock’s win ratio method, this allows death to be interpreted as a participant outcome and infer if the intervention is significantly better than the standard care having considered the clinical priority.

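### Duration of analgesia counts relief still present at hospital arrival as a completed duration, which pulls any difference between the arms towards zero

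*Protocol article*

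**What the plan says.** Table 3 (Outcomes) defines duration of analgesia: "Measured as the time period in which patient pain scores have consecutively decreased or remained stationary". It adds: "There may be different instances of this per patient". The Mitigations cell for this outcome is empty. The cells for time to perceptible and time to meaningful analgesia say what happens when the threshold is not reached.

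The observation period is fixed in four places:

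- Secondary outcomes lists duration under the group headed "Effectiveness of pain relief and overall patient experience from randomisation to arrival at hospital".
- Table 2 ticks duration only at visit 1, labelled "Baseline/Pre hospital/Hospital arrival".
- Primary outcome says the investigators asked that "pain scores were documented regularly from the point of initial IMP administration to arrival at the hospital", and that "no fixed time interval was specified to record pain scores".
- Trial design and setting states: "The prehospital phase ends once the patient arrives at hospital".

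On the model, Data analysis says: "For continuous secondary outcomes, analysis will be carried out in a similar way to the primary outcome". The same section names linear regression for the primary outcome.

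**The concern.** A duration of relief is complete only once relief has been seen to end. Here scoring stops at hospital arrival. For a patient whose run is still going at the last score, the recorded value is only a lower bound on the duration. Linear regression has no way to mark it as such and treats it as complete.

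The error does not fall equally on the two arms. The arm with longer relief has more patients still relieved at arrival, so more of its values are cut short. The difference in means is pulled towards zero. Duration is a named effectiveness outcome, and a small difference could be reported as the two drugs lasting about equally long when the data cannot show that.

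**Working it through.** **The plan's own figure.** The article states no figure for duration. Its sample size reproduces: n per arm = 2 × SD² × (1.960 + 1.282)² / difference² = 2 × 9 × 10.51 / 1 = 189.1, or 190 evaluable. With 15% loss, 189.1 / 0.85 = 222.5, so 223 per arm and 446 in total. It is powered on the primary outcome, so this point does not touch it. The 190 evaluable per arm is carried forward.

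**Inputs that must be assumed.** The article gives no duration of relief and no time from first dose to arrival (the window). The ranges below are illustrations.

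**Closed form.** If relief lasts an exponential time with mean m and the window is fixed at W, the mean of the cut-off value is m × (1 − exp(−W/m)).

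- 15 v 20 min, W = 60: 14.7 v 19.0. The true difference of 5.0 appears as 4.3, so 86% remains.
- 30 v 60 min, W = 60: 25.9 v 37.9. The true difference of 30 appears as 12.0, so 40% remains.
- 60 v 120 min, W = 30: 23.6 v 26.5. The true difference of 60 appears as 2.9, so 5% remains.

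**Simulation.** Window lognormal with log-SD 0.35; true duration Weibull with shape 1 (exponential) or 2; recorded value = the smaller of duration and window; 400,000 patients per arm and setting.

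| True means (min) | Median window (min) | Share of difference left, shape 1 | Shape 2 |
|---|---|---|---|
| 15 v 20 | 60 | 83% | 98% |
| 20 v 30 | 60 | 68% | 90% |
| 30 v 45 | 60 | 49% | 70% |
| 30 v 60 | 60 | 41% | 59% |
| 45 v 90 | 60 | 26% | 33% |
| 60 v 120 | 60 | 17% | 19% |
| 20 v 30 | 30 | 36% | 51% |
| 30 v 45 | 30 | 21% | 26% |
| 60 v 120 | 30 | 6% | 4% |
| 30 v 45 | 90 | 68% | 90% |
| 60 v 120 | 90 | 30% | 40% |

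What governs the loss is the longer arm's mean relative to the window. At a third of the window, 2% to 17% is lost; at half, 10% to 32%. At equality, 36% to 59% is left over all settings run, so about half is lost. Once the longer mean exceeds the window by a third or more, at most 40% is left.

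**Detectability.** A shrunken difference can still be found. For 45 v 90 min with a 60-min window, power from comparing cut-off means at 190 per arm stays near 1.00. For 120 v 240 min with a 30-min window it falls to 0.36 (shape 1) or 0.08 (shape 2).

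**With censoring at arrival.** By the Schoenfeld formula, events needed for 90% power = 4 × (1.960 + 1.282)² / (ln HR)²: 88 for a hazard ratio of 0.50 and 256 for 0.67. Expected events = 190 × (2 − the sum of the two proportions still relieved at arrival). Exponential cases:

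- 30 v 45, 60-min window: 190 × (2 − 0.15 − 0.27) = about 300 events; power 0.94, against 0.91 for cut-off means.
- 60 v 120, 30-min window: 190 × (2 − 0.60 − 0.77) = about 120 events; power 0.97, against 0.75.
- 120 v 240, 30-min window: 190 × (2 − 0.77 − 0.88) = about 66 events; power 0.81, against 0.36.

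The gain is small when few patients are censored and large when many are. These figures assume proportional hazards and do not include patients who never obtain relief.

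**The case against.** The strongest reply is that the window is declared. The article places duration among outcomes that end at arrival, and relief within the prehospital period is a legitimate target. Randomisation balances journey times. Nothing is contradictory, and an analysis plan that is not shown may set the handling of ongoing runs. This stands in part: the limit to the prehospital period is no fault. But the article does fix a definition and a model for continuous secondary outcomes, and together they treat cut-off values as complete. Balanced journeys prevent confounding, not the shrinkage. It is also fair that the model sentence is generic, and that with several runs allowed per patient the outcome is not plainly one continuous value.

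A reader might go further and infer three things that the documents do not support:

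- **That the outcome is really journey time.** The recorded value is the length of a run of non-rising scores. It includes time on scene, ends at any one-point rise even in a well-relieved patient, and can occur more than once. The simulation simplifies this definition.
- **That a real difference is mostly hidden, or that similar durations are the likely result.** The loss depends on figures the article does not give, and even a shrunken difference is often detectable.
- **That dosing time uses up the window.** The Dosing regime section titrates to effect and stops once relief is adequate, so the full course is for patients not yet relieved. Falling scores during dosing also count within a run.

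A simple remedy that starts the clock at first relief has its own weakness: it would compare only responders, a group formed after randomisation. The fix below avoids that.

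**Conclusion.** The point holds in a limited form. As defined and modelled, relief still present at the last prehospital score is counted as finished, which biases the arm difference in duration towards zero. The direction follows from the article's own text. The size does not: it is small if relief is clearly shorter than the time from first dose to arrival. It reaches about half the difference or more once relief lasts about as long as that time, or longer, in at least one arm. These sizes rest on assumed Weibull durations and lognormal windows. The documents do not support saying that the outcome merely measures journeys or that a difference will be missed. Only this secondary outcome is affected. A correction is worth making because it is cheap and protects against reading a small difference as equal duration.

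**What to change.** Define one duration per patient: from the first score showing the plan's own 20% reduction to the first later score at which that reduction is lost. Right-censor patients still relieved at their last score on or before hospital arrival. Keep all randomised patients in the comparison by counting those who never reach 20% as zero duration, and report their proportion by arm.

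Compare arms with Kaplan-Meier curves and either a Cox model or restricted mean time, adjusted for the planned covariates (age, gender, weight, prior IV paracetamol). A block of zeros may strain proportional hazards, so restricted mean time to a horizon set in advance may be the safer summary. If Cox is used, state how zero times are entered. Report the proportion censored by arm, and word the conclusion as maintenance of relief up to hospital arrival.

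The cost is wording in the outcome definition and analysis, with no new data and no change to the sample size. A median may not be reached, so the result may be a hazard ratio or restricted mean instead of a mean duration. Loss of relief is timed only as finely as the unfixed scoring intervals allow. Censoring at arrival also assumes that, within an arm, arrival time is unrelated to when relief would have ended. Since Table 1 shows 362 of 446 already recruited and the statistician can link packs to allocation, date the change and make it before durations are examined by arm.

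### Duration of analgesia counts unchanged severe pain as analgesia; TOTPAR gives no value for no relief, and time to peak has no rule for patients whose pain never falls

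*Protocol article*

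**What the plan says.** The definitions are in Table 3 under Outcomes, which the article presents as the place where outcome definitions and calculation methods are set out.

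- **Duration of analgesia:** "Measured as the time period in which patient pain scores have consecutively decreased or remained stationary", with the remark "There may be different instances of this per patient". The table does not say whether the first, the longest or the summed spell is used.
- **TOTPAR:** a time-weighted sum in which the relief score "is the pain relief score measured as defined below on a scale of 1 to 3". The lowest category is given by "We measure minimal pain relief as 1.8 (1.7–1.9) change in pain score"; much relief is 4.0 (3.9–4.1) and very much relief is 5.2 (5–5.4). A percentage set follows: 20.3 (19–21.6), 44.4 (43.2–45.6) and 56.1 (53.9–58.4). The table does not say which set governs.
- **Time to peak analgesia:** "Measured as the time when lowest NRS pain score, relative to initial pain score, is achieved minus time of first administration". Its mitigation cell is empty.
- **Time to perceptible and to meaningful analgesia**, by contrast, each have a non-responder rule: "If 20% change not achieved, we will score this as perceptible analgesia not achieved" and "If 44% change not achieved, we will score this as meaningful analgesia not achieved".

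The Data analysis section says that continuous secondary outcomes are analysed like the primary outcome, that is, by linear regression. Pain scores are irregular in time: under Primary outcome, "no fixed time interval was specified to record pain scores".

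**The concern.** An outcome called duration of analgesia should be short or zero for a patient who gets none. Under this definition it need not be, because a flat line at severe pain satisfies the wording for as long as it is observed. A large fall followed by a one-point rise ends the spell while the patient is still well relieved. The outcome can therefore give a non-responder as much duration as a responder, or more. The Background says that many patients are left with inadequate relief by current treatment, so such patients should be expected.

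TOTPAR and time to peak raise a related but weaker question: what value does a patient with no improvement receive? The text does not say, and the answer changes the outcome. These are effectiveness outcomes that will be reported beside SPID, so a value that does not track relief could blur or contradict the main result.

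**Working it through.** The plan gives no figure for these outcomes that could be reproduced. Its sample size of 446 rests on the primary outcome and does not enter here. The check applies the Table 3 wording to example series scored at 0, 15, 30, 45 and 60 min. **The series are assumptions, not trial data.** The initial score is taken at first administration unless stated otherwise.

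**Duration.** A run continues while each score is no higher than the one before.

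| Series | Runs (min) | First / longest / sum | SPID |
|---|---|---|---|
| 9, 9, 9, 9, 9 (flat) | 60 | 60 / 60 / 60 | 0 |
| 8, 10, 10, 10, 10 (worse, then plateau) | 45 | 45 / 45 / 45 | −2.0 |
| 9, 5, 3, 3, 3 (lasting responder) | 60 | 60 / 60 / 60 | 5.5 |
| 9, 4, 3, 4, 3 (responder, one-point rise) | 30 and 15 | 30 / 30 / 45 | 5.5 |

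SPID is the sum of (interval in hours) × (initial score − current score). For the second row it is 4 × 0.25 × (−2) = −2.0. For the last it is 0.25 × (5 + 6 + 5 + 6) = 5.5. The flat patient ties with the lasting responder. The flat patient exceeds the fluctuating responder, and the worsened patient equals or exceeds that responder, whichever spell is used.

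**TOTPAR over one hour.** The flat and the worsening patient never reach a 1.8-point fall.
- If 1 is the floor: 4 × 0.25 × 1 = 1.0, the same as an hour of minimal relief, against a maximum of 3.0.
- If 1 is not forced, their relief score has no stated value.

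**The two TOTPAR cut-off sets.** Entry requires a score of at least 7. Baselines 7 to 10 with later scores from 0 up to the baseline give 8 + 9 + 10 + 11 = 38 integer pairs. Each pair was classified by both sets.
- Point estimates as thresholds (1.8 / 4.0 / 5.2 points; 20.3 / 44.4 / 56.1%): 5 pairs differ, namely 10→8, 10→6, 8→3, 7→3 and 7→2. For example, 7→3 is 4 points (much) but 4/7 = 57.1% (very much).
- Lower limits of the printed ranges (1.7 / 3.9 / 5.0 points; 19 / 43.2 / 53.9%): 3 pairs differ, namely 10→6, 10→5 and 7→3.

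**Time to peak.** The result for a non-responder depends on two conventions that the text does not state.
- Initial score eligible as the lowest: a patient who only worsens (7, 8, 9, 9, 10) gets 0 min, or −5 min if the initial score was taken 5 min before the drug. A flat patient gets 0 or −5 min with the first tie, and 60 or 55 min with the last.
- Only post-dose scores eligible: the worsening patient gets 15 min, a positive value, but still earlier than the 30 min (first tie) of the responder at 9, 5, 3, 3, 3.

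**The case against.** A reader might infer that all three rows score patients without relief as having analgesia, and that all three comparisons are therefore biased towards no difference or the wrong direction. The documents do not support that.

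- **TOTPAR.** Minimal relief is tied to a 1.8-point change, so a patient with no change does not meet it. A natural reading is that such a patient contributes nothing. The 1.0 per hour arises only if 1 is forced as the floor. Even then, no non-responder outscores a responder over the same time: the contrast is compressed but not reversed.
- **Cut-offs.** The count of 5 treats the point estimates as hard limits. It would also be tempting to say that a fall from 10 to 8 meets the 20% perceptible rule but fails minimal relief. However, 20% lies inside the printed 19–21.6 range, so that example is not firm. What stands is that two sets are given, no rule chooses between them, and they conflict under either reading.
- **Time to peak.** The wording can be read as making the initial score only the comparator, in which case the time is positive. Zero or negative values need the initial score to be eligible as its own minimum and, for flat scores, the first tie. What stands is the missing non-responder rule.
- **Size of bias.** No responder rates or arm differences are available, so no bias can be quantified.

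It can also be said that a detailed analysis plan, not shown, may settle the derivations. That has some force for the unstated TOTPAR value and the peak convention. It has little for duration, where the article states a definition and that definition gives the wrong answer. The authors may have meant stationary after a fall, but the text does not say so.

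**Conclusion.** The point holds fully for duration of analgesia. As written, an hour of unchanged severe pain counts as 60 min of analgesia, worsening followed by a plateau can count as 45 min, and a responder's spell is broken by a one-point rise. The outcome also lacks the single value per patient that the planned regression needs.

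For TOTPAR the finding is narrower: no value is stated for less than minimal relief or worsening, and the two cut-off sets classify 3 or 5 of 38 score pairs differently. For time to peak it is a missing not-achieved rule, so a patient who never improves still receives a time set by convention.

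The minutes rest on assumed series and a literal reading of Table 3. The pair counts rest on integer scores, each pair counted once; they are not frequencies expected in the trial. The primary outcome, its analysis and the sample size are untouched. The change should be made because the duration rule gives a wrong result when followed and is cheap to correct.

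**What to change.** - **Duration:** derive one value per patient that requires a fall from the initial score. One option is the time at or beyond the trial's own 20% perceptible threshold, set to 0 if never reached and censored at hospital arrival. In the examples, with each score held until the next, both responders then get 45 min (15 to 60 min, still relieved at the last score) and the flat and worsened patients get 0. Other thresholds are defensible. State how censoring at arrival is handled, since plain linear regression does not allow for it.
- **TOTPAR:** score 0 for less than minimal relief or worsening, and name one cut-off set. The percentage set sits closest to the 20% and 44% rules used elsewhere in the table. State whether the point estimates or the range limits are the thresholds.
- **Time to peak:** treat as not achieved when the score never falls below the initial score, as in the perceptible and meaningful rows, and state how ties are resolved.

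The cost is revised wording in the outcome table and analysis plan, and revised derivation code. The pain scores already collected suffice. The changes should be fixed before the allocation is linked to the outcomes.
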